### Trial design and setting

This protocol was developed in accordance with the SPIRIT 2013 statement (S1 File). Fig 1 shows the SPIRIT schedule of enrollment, interventions and assessments. This single-centre, open-label pilot randomized trial will be conducted at the University of Alberta hospital, a tertiary care hospital located in Edmonton, Alberta. Participants will be randomized in a 1:1 ratio to either the Intervention Arm (receiving MyIBDDiet app for the entire duration of the study, i.e., 60 days) or the Control Crossover Arm (receiving usual care as per treating physician for the first 30 days followed by MyIBDDiet App for the latter half of the study) (Fig 2). Outcomes of interest will be assessed at baseline, 1 month, 2 months, and at 6 months follow-up. The 6-month timepoint will allow for assessment of persistence of behavioral and diet quality changes.

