### Sample size

We aim to recruit 40 people living with IBD (20 in each arm). As this is a pilot feasibility and usability study, a formal power calculation was not done. The sample size of n = 40 (n = 20 each arm) is based on established recommendations for pilot trials, where it has been suggested that a minimum of 12–30 participants per arm are sufficient to estimate the variance required for a future power calculation [40,41]. The results of this pilot study will inform the sample size calculation for a future larger, multi-centre randomized trial to evaluate efficacy of MyIBDDiet App. Participants will be recruited for semi-structured interviews until thematic saturation is reached.

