### Statistical analysis plan

The main analytical steps in this study include descriptive statistics, pre-post comparisons, and between-group comparison tests. All quantitative analyses will be conducted on an intention-to-treat (ITT) basis, including all participants who undergo randomization [55]. This pilot randomized study will be conducted over 60 days, comprising two 30-day periods of app use.

Primary and secondary quantitative outcomes: To account for the repeated measures (Baseline, Day 30, Day 60, Day 180) and the crossover study design, we will utilize Linear Mixed Models (LMM) [56,57]. This approach is preferred as it handles missing data robustly via Restricted Maximum Likelihood (REML) estimation and accounts for within- subject and between-subject variability. The model will include “Group”, “Time” and “Group X Time” interactions as fixed effects, with a random intercept for each participant. In the event of model non-convergence, the random effects structure will be simplified.

Handling of missing data: We anticipate an attrition rate of 10–15%. Linear Mixed Models allow for the inclusion of participants with missing timepoints under missing at random assumption. If missing data exceeds 20%, Multiple imputations by chained Equations (MICE) will be performed [58].

Effect size and Variance: As this is a pilot study, the focus of analysis is not solely on p-values, but on point estimates and confidence intervals. We will calculate Cohen’s d effect sizes for change in quantitative outcomes to provide the necessary variance and magnitude of effect estimates required for a power calculation in a future larger trial. We will be using SPSS version 29.0.2.0 (20) for statistical analyses.

Semi-structured interviews: The interviews will be transcribed verbatim. Thematic analysis will be done independently by two researchers using Nvivo which is a qualitative data analysis software and any conflicts will be resolved by a third reviewer who is a senior gastroenterologist and principal investigator [59].

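### The mixed model treats baseline as a free outcome, so the app effect becomes a difference in changes and its interval is wider than the baseline data allow

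*Protocol article*

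**What the plan says.** The Statistical analysis plan section lists the responses as "repeated measures (Baseline, Day 30, Day 60, Day 180" and fixes the model: "The model will include “Group”, “Time” and “Group X Time” interactions as fixed effects, with a random intercept for each participant". It names no baseline covariate and no constraint on the baseline means. It then plans Cohen's d "effect sizes for change in quantitative outcomes", which points to the same contrast, a difference in changes.

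The section gives the aim of these estimates: "the focus of analysis is not solely on p-values, but on point estimates and confidence intervals". They are meant to supply variance and effect size for a later trial.

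On size and allocation, the Sample size section says "We aim to recruit 40 people living with IBD (20 in each arm" and that "a formal power calculation was not done". The Trial design and setting section says "Participants will be randomized in a 1:1 ratio". Controls receive usual care for 30 days and then the app, so Day 30 is the only visit with a randomised comparison of app against usual care.

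**The concern.** Because baseline is a response and the Group term is free, the model fits a separate baseline mean in each arm. With complete data, the Day 30 Group × Time coefficient is then exactly the difference between arms in mean change. That subtracts the observed baseline imbalance with a slope of 1.

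Randomisation has already set the expected imbalance to zero. The efficient correction uses the regression slope of Day 30 on baseline, which equals r when the two variances are equal. A slope of 1 over-corrects whenever r is below 1. With 20 per arm, the chance difference in baseline means has a standard deviation of √(2/20) = 0.32 SD, so the over-correction matters.

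What is lost is precision on the secondary outcomes that have a baseline value: diet quality, disease activity, quality of life and urine markers. The plan presents estimates and intervals as its main product, and precision lost at Day 30 cannot be recovered at later visits, when both arms have had the app.

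**Working it through.** **Inputs from the Protocol article.** 20 per arm, 1:1 randomisation; responses at baseline and Days 30, 60 and 180; a random intercept, which implies equal variances and one common correlation r between visits; attrition of 10–15%, which leaves 18 to 17 per arm (20 × 0.90 = 18; 20 × 0.85 = 17).

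**Assumptions.** The outcome SD is set to 1. The correlation r is not in the document, so a range is shown. No planned power or interval width is stated, so there is no figure to reproduce.

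**Formulas, n per arm.**
- Planned contrast (difference in changes): Var = 4(1 − r)/n
- Baseline-adjusted contrast (common baseline mean, or baseline as covariate): Var = 2(1 − r²)/n
- Ratio, adjusted to planned: 2(1 − r)(1 + r) / [4(1 − r)] = (1 + r)/2

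**Numbers put in for r = 0.5, n = 20.**
- Planned: √(4 × 0.5/20) = √0.100 = 0.316
- Adjusted: √(2 × 0.75/20) = √0.075 = 0.274
- n per arm at which the planned model matches: 20/0.75 = 26.7

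**Results at n = 20 per arm, in SD units (half-width = 1.96 × SE).**

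| r | SE planned | SE adjusted | Variance ratio | 95% half-width, planned vs adjusted | n per arm for planned model to match |
|---|---|---|---|---|---|
| 0.3 | 0.374 | 0.302 | 0.65 | 0.73 vs 0.59 | 30.8 |
| 0.5 | 0.316 | 0.274 | 0.75 | 0.62 vs 0.54 | 26.7 |
| 0.6 | 0.283 | 0.253 | 0.80 | 0.55 vs 0.50 | 25.0 |
| 0.7 | 0.245 | 0.226 | 0.85 | 0.48 vs 0.44 | 23.5 |
| 0.9 | 0.141 | 0.138 | 0.95 | 0.28 vs 0.27 | 21.1 |

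With 17 per arm the half-widths are 0.67 vs 0.58 SD at r = 0.5 and 0.52 vs 0.48 SD at r = 0.7.

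**Checks.** Exact generalised least squares with all four visits and the random-intercept correlation gave ratios of 0.65, 0.75, 0.85 and 0.95 at r = 0.3, 0.5, 0.7 and 0.9, equal to (1 + r)/2. In 300 simulated trials at each of r = 0.5 and 0.7, fitted by REML, the planned Day 30 interaction equalled the raw difference in mean changes in every data set. The simulated variance ratios were 0.75 and 0.88, and both models averaged close to the true effect of 0.5 (0.48 to 0.49).

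**Against ignoring baseline.** A plain Day 30 comparison has variance 2/n, hence an SE of 0.316 at n = 20. Below r = 0.5 the planned contrast is worse than that (0.374 at r = 0.3). The adjusted contrast is better at every r above 0, with variance ratio 1 − r² (0.91 at r = 0.3, 0.19 at r = 0.9).

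**Illustrative power**, for an assumed difference of 0.5 SD at two-sided 5% and 20 per arm: 35% vs 45% at r = 0.5, and 53% vs 60% at r = 0.7.

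**The case against.** The planned model is valid and unbiased under randomisation, so this is lost efficiency rather than error. The primary outcome is presumably untouched, because the usability and acceptability ratings of the app should have no pre-app value. No power figure is made wrong, since none is stated. All of this stands and limits the weight of the point.

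The contrast to be reported is not named, and the same model could yield a plain Day 30 difference in means. That does not rescue the plan: this contrast is also less precise than the adjusted one at every r above 0. Nor is the point a detail left to a fuller document, because the article fixes the responses and the fixed effects, and a fuller plan would have to change them.

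The formulas are slightly optimistic for small samples. Estimating the slope in an ANCOVA costs an expected factor of 1 + 1/(2n − 4) = 1 + 1/36 = 1.028 at n = 20 per arm. The ratios at r = 0.5, 0.6 and 0.7 become about 0.77, 0.82 and 0.87, and the gain at r = 0.5 is worth about 30% more patients instead of 33%. At r = 0.9 little remains.

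The most substantive objection concerns the order of events. A common baseline mean is guaranteed only if baseline is measured before the participant knows the arm. The trial is open-label with self-reported outcomes, and the Enrollment and randomization section does not make the order clear. It does not show that baseline follows allocation, but the remedy should carry this condition.

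**Conclusion.** The concern holds. As written, the model estimates the app effect as a difference in changes and gives up precision that the collected baseline values could supply. The variance saving is 25% at r = 0.5, 15% at r = 0.7 and 5% at r = 0.9, slightly less once slope estimation is counted. These sizes rest on assumed correlations and on equal variances at baseline and Day 30.

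The fault is wider intervals, not bias, and it is confined to secondary outcomes with a baseline measurement. The change should be made: intervals are the stated focus, the sample is 40, and Day 30 is the only randomised comparison of app with usual care.

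**What to change.** Keep baseline among the responses but drop the Group term at baseline: fit Time plus Group × post-baseline visit (Days 30, 60 and 180), so that both arms share one baseline mean. Alternatively, model Days 30, 60 and 180 with the baseline value as a covariate by visit.

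The first form suits the stated intention-to-treat set better. It keeps participants with a missing baseline value or with baseline only, whereas the covariate form loses them unless values are imputed. This matters under the expected attrition, and for C-reactive protein and calprotectin, which are collected as part of standard care and may not be available for everyone at baseline.

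Apply the model to every secondary outcome with a baseline measurement. State that baseline assessments are completed before allocation is disclosed; if that cannot be ensured, the common-mean constraint is not guaranteed by design. Report the adjusted Day 30 difference with its confidence interval, together with the outcome SD and the baseline-to-Day 30 correlation, which the later trial will need for its sample size.

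The cost is a change of analysis wording, with no added visits or measurements.

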### Microbial and metabolomic analysis

Microbial diversity will be evaluated through both α-diversity and β-diversity metrics, specifically using the Shannon index and Bray-Curtis dissimilarity, respectively. Metabolomics datasets will be analyzed using the KEGG database [60] to facilitate pathway mapping and biological interpretation.

Principal Coordinates Analysis (PCoA) will be employed to visualize and compare microbiome profiles pre- and post-intervention at baseline, day 30 and day 60, as well as between usual care and MyIBDDiet app groups at baseline and day 30. Univariate analysis, specifically ANOVA, will be applied to identify statistically significant features across groups. In addition, multivariate analysis via Principal Component Analysis (PCA) will be employed to visualize and compare metabolic profiles between pre- and post-intervention samples, as well as between subjects in usual care versus MyIBDDiet app group. As this is a pilot study with a small sample size, multivariable analyses and PCA will be strictly exploratory.

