### Primary, secondary and exploratory outcomes

The primary outcome of usability will be evaluated using a mixed-method quantitative [mHealth App Usability Questionnaire (MAUQ) and Theoretical Framework of Acceptability (TFA)] and qualitative (semi-structured interviews) approach.

Secondary outcomes of interest include clinical efficacy evaluated by change in diet quality [Mini-EAT questionnaire, Automated Self-administered 24-Hour Dietary Assessment Tool (ASA-24), Healthy Eating Index (HEI), Mediterranean Diet Serving Score (MDSS)], urine sodium and chloride (biomarkers of processed food intake), changes in disease activity [Patient Reported Outcome (PRO2 UC and PRO3 CD), C-reactive protein, fecal calprotectin] and changes in quality of life [EQ-5D, SIBDQ]. Behaviour changes and diet knowledge will be assessed objectively by measuring changes in diet quality scores, changes in the nutrient intake data obtained from ASA 24 and subjectively by assessing responses to individual questions on changes in diet in the semi-structured interview. To assess safety, systematic monitoring of adverse events and serious adverse events will be done at each time point and in between time points if symptoms worsen.

Exploratory outcomes include changes in fecal microbiome and serum and fecal metabolites to correlate with change in diet and disease activity.

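### Whole microbiome and metabolite profiles are to be compared by PCoA and PCA alone, which give no estimate or test and ignore participant pairing, so a real within-person shift could easily be missed or a chance one over-read

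*Protocol article*

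**What the plan says.** The section on primary, secondary and exploratory outcomes sets the target: "Exploratory outcomes include changes in fecal microbiome and serum and fecal metabolites to correlate with change in diet and disease activity".

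The section on microbial and metabolomic analysis gives the methods:

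- **Diversity measures:** α- and β-diversity, "specifically using the Shannon index and Bray-Curtis dissimilarity, respectively". No model or test is attached to either.
- **Whole microbiome profiles, before versus after:** "Principal Coordinates Analysis (PCoA) will be employed to visualize and compare microbiome profiles pre- and post-intervention at baseline, day 30 and day 60".
- **Whole microbiome profiles, between arms:** the same ordination, "as well as between usual care and MyIBDDiet app groups at baseline and day 30".
- **Whole metabolite profiles:** "multivariate analysis via Principal Component Analysis (PCA) will be employed to visualize and compare metabolic profiles between pre- and post-intervention samples", and also between usual care and app.
- **Single features:** "Univariate analysis, specifically ANOVA, will be applied to identify statistically significant features across groups".
- **Status:** the section closes by calling multivariable analyses and PCA strictly exploratory because the pilot is small.

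The statistical analysis plan section of the article specifies a linear mixed model with a participant random intercept, but under a heading that names primary and secondary quantitative outcomes only. The same section puts the emphasis on point estimates and confidence intervals.

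**The concern.** PCoA and PCA are unsupervised. They rotate the data onto the axes of greatest total variation without knowing which samples are before or after the app, which arm they belong to, or which share a participant. They yield coordinates for a plot, not a contrast with an interval or a p-value. Giving them the task of comparing profiles leaves that comparison to visual judgement.

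The outcome is change, and change is a within-person quantity. If people differ from one another much more than they differ from themselves a month apart, the leading axes mostly describe who the person is. A common shift across participants may then be almost invisible on the plot. Conversely, two small clouds always separate a little by chance, and nothing in the stated method says how much is too much. The randomised Baseline-to-Day-30 comparison has the same weakness.

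At stake is the return on the 16S sequencing and the stool and serum metabolomics. The whole-profile question may be left with pictures that support neither a finding nor a planning estimate for the later trial.

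**Working it through.** **No figure to reproduce.** The article gives no power, alpha, effect size or variance for these outcomes. The only usable inputs are 40 participants (20 per arm) and expected attrition of 10-15%: 20 × 0.90 = 18 and 20 × 0.85 = 17 per arm, or 36 and 34 overall. Everything biological below is an assumption.

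**Set-up (one arm, before and after).** 80 taxa with log-normal abundances (log-SD 2 across taxon means), 10,000 reads per sample, and Bray-Curtis distances D. Between-person log-SD was 1.0 or 1.5 and within-person log-SD 0.75 or 1.0. A common shift of 0, 0.5 or 0.8 log units was placed on 16 taxa. There were 17 or 20 pairs, 200 runs per setting, 199 permutations per run, and alpha 0.05.

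**Formulas.** With G = J(−½D²)J (J the centring matrix) and g = −1 before, +1 after:

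- before-after share = (gᵀGg / 2n) / trace(G)
- p = (1 + number of permuted values ≥ observed) / 200
- paired test: swap before/after labels at random within each person
- unpaired test: shuffle all 2n labels

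The average share under relabelling follows by algebra. It is (1 − person share)/n when labels are swapped within person and 1/(2n − 1) when pairing is ignored. For n = 20 the latter is 1/39 = 2.56%.

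**Results for 20 pairs.**

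| Between / within log-SD | Shift | Person share | Before-after share | Paired yardstick | Separation on axes 1-2 (SD) | Paired test detects | Unpaired test detects |
|---|---|---|---|---|---|---|---|
| 1.5 / 0.75 | 0 | 85.8% | 0.76% | 14.2/20 = 0.71% | 0.18 | 3.5% | 0% |
| 1.5 / 0.75 | 0.5 | 85.2% | 1.08% | 14.8/20 = 0.74% | 0.23 | 27% | 0% |
| 1.5 / 0.75 | 0.8 | 84.4% | 1.63% | 15.6/20 = 0.78% | 0.28 | 58.5% | 1% |
| 1.5 / 1.0 | 0 | 78.9% | 1.06% | 21.1/20 = 1.06% | 0.22 | 4.5% | 0% |
| 1.5 / 1.0 | 0.5 | 78.5% | 1.27% | 21.5/20 = 1.08% | 0.24 | 11% | 0% |
| 1.5 / 1.0 | 0.8 | 78.2% | 1.75% | 21.8/20 = 1.09% | 0.29 | 36% | 0.5% |
| 1.0 / 1.0 | 0 | 70.5% | 1.42% | 29.5/20 = 1.48% | 0.27 | 5.5% | 0% |
| 1.0 / 1.0 | 0.5 | 70.0% | 1.97% | 30.0/20 = 1.50% | 0.35 | 20% | 1% |
| 1.0 / 1.0 | 0.8 | 69.1% | 2.81% | 30.9/20 = 1.55% | 0.43 | 46% | 10.5% |

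With 17 pairs the paired test detected the 0.5 shift in 10-19% of runs and the 0.8 shift in 33-56%; the unpaired test managed 0-1% and 0.5-2%.

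**Reading the table.**

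1. On the plot, a 0.5 shift at 20 pairs moves the centroids from 0.18 to 0.23, 0.22 to 0.24 or 0.27 to 0.35 SD apart. That is an extra 0.02-0.08 SD, which the eye could not reliably tell from chance.
2. The real before-after share exceeds the paired yardstick in every shifted row. It exceeds the unpaired yardstick of 2.56% only in the last, so the information lies in the pairing.
3. At one-arm size even the paired test usually misses the 0.5 shift.

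**Pooling both arms.** A similar simulation at 35 pairs (log-SD 1.0 across taxon means) gave paired detection of 36-85% for the 0.5 shift and 88-100% for the 0.8 shift, with 4-6% when there was no shift. Ignoring pairing gave 0-2% and 0-52%. These pairs come from different calendar periods (Baseline to Day 30 in the early arm, Day 30 to Day 60 in the delayed arm), so the contrast is not randomised.

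**The case against.** The strongest reply is that this is a condensed article and that the test behind an ordination is a detail commonly left to a fuller plan. Plotting Bray-Curtis distances does not preclude a PERMANOVA, and the text nowhere says that the comparison will be by eye. That stands against any claim that the investigators will run no test. It does not remove the point, because the article does not simply leave the method open: it names ordination as the means of comparing profiles, and that wording would need changing even if a test exists elsewhere.

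Three stronger readings are tempting, and the documents do not support them.

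- **A real shift would be missed.** That depends on variance components the documents do not give. The calculations show only that it could easily happen. The unpaired permutation test is an illustration; the protocol does not propose it.
- **The change outcome goes unanswered.** The Shannon index summarises community diversity and the ANOVA addresses single features, so only the whole-profile part is poorly served. The opening of the statistical analysis plan section also lists pre-post and between-group comparisons in general terms.
- **Overlapping clouds will be reported as no effect.** Nothing in the text says so, and the section labels PCA and multivariable analyses strictly exploratory.

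That label limits what may be claimed. It does not turn a plot into an estimate.

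**Conclusion.** The point holds in limited form. For whole microbiome and metabolite profiles, before versus after and between arms, the stated comparison is ordination only. It supplies no effect estimate or test and makes no use of participant pairing, although the outcome is change. A genuine within-person shift could easily be overlooked, and a chance separation over-read.

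The size is illustrative. Across the assumed settings, paired testing detected a real shift in anything from 10% to 100% of runs, against 0-52% without pairing. The direction was the same in every setting tabulated; the level rests wholly on assumed variances, shift sizes and number of pairs, and should not be quoted as a single figure. Metabolite data were not simulated; there the argument rests on the nature of PCA.

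Severity is minor. These are exploratory outcomes in a 40-person usability pilot, and no primary or secondary conclusion depends on them.

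**What to change.** Keep PCoA and PCA as displays, and state these as the comparisons, all labelled exploratory:

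1. **Randomised contrast.** Compare the arms on each participant's Baseline-to-Day-30 change, for example through the arm-by-time term of a PERMANOVA on Bray-Curtis distance (Euclidean distance for metabolites), permuting arm labels across participants. A comparison of arms at Day 30 alone would not use baseline and would not test change.
2. **Before-after contrast.** Run a PERMANOVA with permutations restricted within participant, using the last sample before the app and the next one on it. Describe it as an uncontrolled before-after comparison, since it cannot separate the app from time.
3. **Link to diet and disease activity.** Correlate within-person change in the Shannon index and in the leading metabolite components with change in diet scores and in disease activity.

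The cost is a few sentences of analysis text and some scripting on data already planned, with no new samples or visits. The article names SPSS, and this part will probably need other software. Recruitment was anticipated from March 2026 to March 2028, with analysis complete by August 2028, so the wording can be settled before results are seen. At this sample size the added tests may still be inconclusive, so report effect sizes with their uncertainty rather than p-values alone.
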